#### Pharmacist-led de-escalation

Another algorithm will identify CAP patients meeting study criteria with negative culture results for more than 48 h, generating a list for the clinical pharmacist. The pharmacist will audit the daily alerts on weekdays at a centralized location and assess patient clinical stability using the 2019 ATS/IDSA criteria for clinical stability:A.Resolved vital sign abnormalities (temperature ≤ 37.8 °C, heart rate ≤ 100 beats/min, arterial oxygen saturation ≥ 90% or pO_2_ ≥ 60 mmHg on room air, systolic blood pressure ≥ 90 mmHg, and respiratory rate ≤ 24 breaths/min),B.Normal mental status (as deemed by the clinician), andC.Ability to maintain oral intake [6].

For clinically stable patients, the pharmacist will recommend antimicrobial de-escalation to clinical providers via secure electronic medical record chat, phone call, or page. De-escalation in this context means stopping all ESA agents (anti-MRSA/anti-pseudomonal) but continuing other antibiotics. The pharmacist’s recommendations will be based on a protocol developed by the Cleveland Clinic Health System’s Antimicrobial Stewardship committee, outlining four possible clinical scenarios: (a) positive culture, (b) negative culture, (c) pneumococcal UAT results, and (d) viral test results.

Pharmacist-led de-escalation efforts will be supported by educational initiatives targeting hospitalists, including presentations about the study and audit-and-feedback for adherence to pharmacist recommendations. Site champions at each hospital will ensure intervention fidelity and encourage physician receptiveness to pharmacist messages/calls.

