To address the non-adherence limitation, we will conduct two secondary analyses [17]. First, we will perform an as-treated analysis, comparing outcomes among those who receive the treatment versus those who receive control, regardless of randomization. Second, we will calculate complier average causal effect (CACE) estimation, which uses randomization as an instrument to account for unobserved confounding and provides a randomization-respecting estimate [18]. CACE estimates the intention-to-treat effect in the subgroup of participants who always comply with their treatment allocation. In addition, we will use per-protocol analysis, comparing those who comply with their random allocation in the treatment group with all the controls. We will use an inverse probability weighting approach to minimize selection bias [19]. All the secondary analyses will use the framework of mixed-effects (hierarchical, two-level) models as described above for the primary ITT analyses.

All continuous secondary outcomes will be analyzed using the same method as the primary outcome. For each secondary outcome, we will adjust for the rate of that outcome in the 12 months prior to the study. Binary outcomes will be analyzed using generalized linear mixed-effects models. All analyses will be conducted using SAS 9.3 (Cary, NC), R-studio (Boston, MA), and STATA (College Station, TX). Our trial will follow the Consolidated Standards of Reporting Trials guidelines, extended for cluster-randomized controlled trials [20].

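### For Aim 2, the per-protocol and as-treated comparisons set patients eligible for de-escalation after 48 h against a comparator that is not so restricted, so both are biased as written

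*Protocol article*

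**What the plan says.** The Data analysis plan names three analyses for non-adherence, all secondary:

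- As-treated: "comparing outcomes among those who receive the treatment versus those who receive control, regardless of randomization".
- Per-protocol: "comparing those who comply with their random allocation in the treatment group with all the controls", followed by the statement "We will use an inverse probability weighting approach to minimize selection bias". The weighting variables are not named there.
- CACE, which "uses randomization as an instrument to account for unobserved confounding and provides a randomization-respecting estimate".

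The section Pharmacist-led de-escalation describes who can receive the intervention. The list is built as follows: "Another algorithm will identify CAP patients meeting study criteria with negative culture results for more than 48 h". Then "For clinically stable patients, the pharmacist will recommend antimicrobial de-escalation to clinical providers". The action itself is defined: "De-escalation in this context means stopping all ESA agents (anti-MRSA/anti-pseudomonal) but continuing other antibiotics". Adherence is mentioned there as "audit-and-feedback for adherence to pharmacist recommendations".

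Eligibility criteria admits adults with an admitting diagnosis of pneumonia and does not require ESA use. Outcomes counts ESA days over the first 21 days of admission, with two agents on one day counted as two days. The covariates listed for adjustment are baseline patient and hospital characteristics. None records ESA use, culture result or stability at 48 h.

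**The concern.** A patient can accept a recommendation to stop ESAs only after meeting several conditions that arise after admission: still in hospital, cultures negative for more than 48 h, clinically stable, and on an ESA. The per-protocol rule keeps such patients on the treated side and puts all controls on the other. Those controls include patients never on an ESA, already off it, discharged or dead before 48 h, culture-positive or unstable. The as-treated rule has the same asymmetry.

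Two distortions follow. ESA days accrued before the flag are charged to the treated side, while many comparators contribute none, so an effective intervention can look harmful. For death and ICU transfer the distortion runs the other way. The treated side consists of people who survived and were stable past 48 h, while earlier deaths, and ICU transfers between 24 and 48 h that rule out stability, fall on the comparison side. That would make de-escalation look safer than it is, and the Discussion says the trial hopes to demonstrate its safety.

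**Working it through.** **The plan's own figure.** The document gives no number for these analyses. The only quantified de-escalation effect is in Sample size and power analysis: 1 day, SD 3, ICC 0.005, 6 versus 6 hospitals of about 1000 patients, coefficient of variation 0.4, power above 99%. Design effect = 1 + ((0.4² + 1) × 1000 - 1) × 0.005 = 6.795. Effective size per arm = 6000/6.795 = 883. Standard error = 3 × √(2/883) = 0.143. Power for 1 day exceeds 99.9%, so the figure reproduces with the 1 day taken undiluted. I use 1 day as the effect in patients who accept.

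**Algebra, reading A (complier = accepted recommendation).** Let p be the share of patients meeting the 48-h conditions, and m_e and m_o the control mean ESA days with and without those conditions. If acceptance is unrelated to prognosis:

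- treated mean = m_e - 1
- mean of all controls = p·m_e + (1 - p)·m_o
- unweighted per-protocol estimate = (1 - p)(m_e - m_o) - 1

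This is positive when m_e - m_o > 1/(1 - p): 1.25 days at p = 0.2, 1.43 at 0.3, 2.0 at 0.5. A total SD of 3 permits a gap of up to 3/√(p(1 - p)), which is 7.5, 6.5 and 6.0 days. The stated SD therefore does not exclude reversal.

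**Simulation, reading A.** Patient-level, 600,000 patients per scenario, no clustering. From the document: 50% acceptance and an effect of about 1 day. Assumed, not in the document: ESA started in 20% to 100% of patients of median severity, about 75% of those still on an ESA at 48 h, about 60% of those eligible, a mean of 3 further ESA days, acceptance independent of prognosis. Simulated control SDs were 2.73 to 3.89, against the stated 3 (Aim 2) and 3.5 (Aim 1). Columns 2 to 5 have half of patients on two agents.

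| ESA start | True effect | Per-protocol | Per-protocol, baseline-weighted | As-treated | Per-protocol, one agent only |
|---|---|---|---|---|---|
| 20% | -1.15 | +3.97 | +3.70 | +4.09 | +3.18 |
| 35% | -1.11 | +3.20 | +2.98 | +3.38 | +2.50 |
| 50% | -1.08 | +2.50 | +2.34 | +2.70 | +1.95 |
| 80% | -1.03 | +1.20 | +1.15 | +1.39 | +0.86 |
| 100% | -0.98 | +0.06 | +0.10 | +0.18 | -0.05 |

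Comparing accepters with controls who meet the same 48-h conditions gave -0.98 to -1.14 in every scenario. CACE gave -0.98 to -1.15.

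There was no reversal when everyone started an ESA and 90% were still on it at 48 h (per-protocol about -0.6), or with a 3-day effect and ESA start of 80% or more (about -0.9 to -2.2).

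**Reading B (never-flagged patients count as compliers, only refusals dropped).** Refusers, who have long ESA courses, leave the intervention side while their counterparts stay among the controls. Per-protocol was -0.29 to -0.62, against ITT of -0.05 to -0.21. Nor is this the effect under full acceptance. At 50% ESA start, two-agent case, the eligible share is 0.21, so full acceptance would give 0.21 × (-1.08) = -0.23, while per-protocol gave -0.55.

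**Weighting.** Under reading A, a patient who does not meet the 48-h conditions has zero probability of receiving the intervention. No weight built on baseline covariates makes accepters represent such patients. The table shows how little those weights move the estimate.

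**Safety outcomes.** The direction follows from the definitions: mortality is counted over 14 and 30 days, and ICU transfer from 24 h after admission. I have not put a size on it.

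**The case against.** The strongest reply is that *comply* is undefined. Allocation is by hospital, and a patient who never becomes eligible has not departed from it. On that reading the reversal and the positivity failure both disappear, and the operational definition may sit in an analysis plan that is not shown. This stands as far as it goes: the direction of the bias depends on the reading. It does not clear the analysis, because reading B is biased in favour of de-escalation, and the comparator of all controls is stated outright rather than left open.

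The magnitude rests on ESA prevalence, duration and stability rates that the document does not give. That also stands. A reader might infer that the sign will reverse; the document supports only that it can. A reader might also infer that every treated patient carries at least two ESA days. It does not say so: the trigger is the duration of negative cultures, not of ESA therapy, and an ESA may start late.

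A reader might further infer that the trial's safety conclusions rest on these analyses. Nothing says so. Thirty-day mortality is compared across the four randomized groups, and the interim safety analyses are by arm.

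Finally, a like-with-like comparison after 48 h selects on post-randomization status. Testing and education may alter who is still on an ESA by then, and its good showing above assumes acceptance unrelated to prognosis. That is a fair limit on the remedy.

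**Conclusion.** The point holds for Aim 2. If compliance or receipt means an accepted recommendation, both analyses bias ESA days upward for the treated side. The sign can reverse when a substantial share of patients are not on an ESA at 48 h. Under the assumptions above, per-protocol ran from about +4 days at 20% ESA start to about zero at 100%, for a true effect near -1. Reversal does not occur when nearly all patients are on an ESA at 48 h, or when the effect is large and ESA use is high. Death and ICU transfer are biased toward apparent safety. If only refusals are dropped, per-protocol exaggerates the benefit. The planned weighting, on the covariates listed, removes little of the bias.

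These are secondary analyses. The primary ITT analysis, CACE, and the rapid-testing aim, where orders are appended at admission, are not affected. The change is worth making but does not threaten the main result.

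**What to change.** 1. Define compliance for Aim 2 as acceptance of a recommendation among eligible patients.
2. At all 12 hospitals, identify from the shared EMR patients with cultures negative for more than 48 h who are on an ESA and meet those stability criteria that can be derived from the record. The existing algorithm covers only the culture condition. Stability is judged by the pharmacist and no ESA filter is stated, so both filters must be added.
3. Restrict both sides of the per-protocol analysis to these patients and count outcomes from the time they qualify.
4. Estimate the acceptance weights within this set, using covariates measured up to that time.
5. Treat the as-treated analysis the same way, or drop it and keep CACE as the main non-adherence analysis.
6. Label the results supportive.

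The cost is revised wording, some EMR programming, and fewer patients in these analyses. Stability can be reconstructed only in part, since mental status is a clinician's judgement. Some selection remains because eligibility is assessed after randomization.

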### Cost analysis

We will conduct a cost analysis from the health system perspective, including only medical costs related to providing care and excluding costs associated with patient time spent seeking care, caregiver time, transportation, or productivity loss. Total direct medical costs of the hospitalization/inpatient encounter will be collected through the Cleveland Clinic finance system. Costs are grouped into different categories, including inpatient, outpatient, laboratory testing, and pharmacy. For the intervention groups, we will also include the cost of rapid diagnostic testing and time cost of the pharmacists, calculated as hourly salary multiplied by the number of minutes pharmacists spent discussing de-escalation with providers. Due to the right-skewed nature of cost data, we will use bootstrap methods to compare median costs between groups [21]. We will draw 1000 bootstrap samples with replacement from each study group and calculate the mean cost difference and 95% confidence interval. Finally, we will employ a generalized linear mixed-effects model (with a log-link function and gamma distribution) to analyze the interventions' effect on total cost, accounting for differences in baseline patient-level characteristics.

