The primary outcome of days on ESA will be analyzed using a linear mixed-effects model, which will include the treatment arm as a fixed effect and a random-intercept at the randomized hospital level. We will adjust for baseline covariates between the intervention and control groups. These covariates include patient age, sex, race, CURB65, Elixhauser index, serum Na, serum glucose, hemoglobin, MRSA nasal swab (yes/no), WBC count, albumin, baseline oxygenation for CAP patients (O_2_ sat off O_2_ or supplemental oxygen delivery device type (vent > bipap > high flow, etc.), max or median respiratory rate on day 1, min SBP on day 1, vasopressors, and comorbidities (chronic pulmonary disease, lymphoma, metastatic cancer, obesity), as well as hospital characteristics in the year prior to study initiation (duration of antibiotics and ESA, AKI, CDI, 14-day mortality, and 30-day mortality, all among CAP patients who would have met study criteria). The primary comparison is to compare the duration of exposure to ESA therapy in the four treatment groups. Interaction between the two interventions will be tested as a secondary analysis. We will consider a two-sided *p*-value < 0.05 statistically significant. As we use a priori stratification (by the type of hospital), we will examine differential intervention effects by each pre-defined stratum. The primary outcome data will be available for every patient since it is recorded in the EHR. In case of missing secondary data, we will assume it is missing at random and a sensitivity analysis will be performed with data imputed via Multiple Imputation by Chained Equations (MICE).

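### The cost bootstrap announces medians but computes a mean difference and makes no provision for the randomised hospitals; the pharmacist and test costs are also incompletely or unevenly defined

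*Protocol article*

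**What the plan says.** All of the following is in the protocol article.

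- **Target of the bootstrap (Cost analysis).** Citing right-skewed costs, the section states that "we will use bootstrap methods to compare median costs between groups". The next sentence reads: "We will draw 1000 bootstrap samples with replacement from each study group and calculate the mean cost difference and 95% confidence interval". The resampling unit is not named.
- **Second method (Cost analysis).** The section closes with a regression: "we will employ a generalized linear mixed-effects model (with a log-link function and gamma distribution) to analyze the interventions' effect on total cost". Its random effect is not named there. The Data analysis plan gives the primary model "a random-intercept at the randomized hospital level".
- **Third method (Data analysis plan).** "All continuous secondary outcomes will be analyzed using the same method as the primary outcome". Total inpatient cost is on the list of secondary outcomes, so this sentence assigns it a linear mixed model.
- **Test cost (Cost analysis).** "For the intervention groups, we will also include the cost of rapid diagnostic testing". The finance data already contain such a category: "Costs are grouped into different categories, including inpatient, outpatient, laboratory testing, and pharmacy". Under Study recruitment and participant identification, control physicians remain free to order any diagnostic test.
- **Pharmacist cost (Cost analysis).** It is "calculated as hourly salary multiplied by the number of minutes pharmacists spent discussing de-escalation with providers". The section Pharmacist-led de-escalation describes more work than that: a weekday audit of the alert list and an assessment of each patient's clinical stability.

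**The concern.** Two things are wrong with the bootstrap step. First, for right-skewed costs a median difference and a mean difference are different quantities, and the text promises one and computes the other. Second, the trial randomises 12 hospitals, and the step says nothing about them. An interval that treats patients within an arm as independent leaves out between-hospital variation, so a chance difference between a few hospitals could look like a cost effect of the intervention. This matters because the bootstrap gives the only cost difference with a confidence interval that the Cost analysis section promises, and the Discussion in the abstract expects success to lead to reduced healthcare costs.

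The cost inputs raise a separate question. If part of the pharmacist's work is not costed, or tests are charged differently by arm, the difference compares unlike quantities however its interval is formed.

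**Working it through.** **Inputs.** From Sample size and power analysis: 12 hospitals, 6 against 6 for each factor; mean cluster size m = 1000; coefficient of variation of cluster size 0.4; ICC 0.001 (Aim 1) and 0.005 (Aim 2), both for days of extended-spectrum antibiotics; Aim 1 effect 0.3 days, SD 3.5, power 83%. From Participating sites: 3 hospitals per arm. *The ICC of cost is not given*, so the two protocol values and an assumed 0.02 are used to show the range.

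**1. The plan's own power figure.** At ICC 0.001:

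- Without allowance for unequal sizes, DE = 1 + 999 × 0.001 = 2.00. Dividing by a relative efficiency of 0.96 for unequal hospital sizes gives DE = 2.08.
- SE = 3.5 × √(2 × 2.08 / 6000) = 0.0922, and 0.3 / 0.0922 = 3.25.
- A noncentral t with 10 df gives power 83.4%, which reproduces the stated 83%.
- Ignoring clustering, SE = 3.5 × √(2/6000) = 0.0639 and power would be 99.7%.

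The sizing therefore treats hospitals as the independent units. The bootstrap step does not carry that over.

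**2. If patients are resampled within arms.** The standard error of the mean difference is too small by √DE. Here the slightly more conservative form DE = 1 + ((1 + 0.4²) × 1000 − 1) × ICC = 1 + 1159 × ICC is used. Coverage of the nominal 95% interval is 2Φ(1.96/√DE) − 1.

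| ICC | DE | SE too small by | Coverage |
|---|---|---|---|
| 0.001 (Aim 1) | 2.16 | 1.47 | 82% |
| 0.005 (Aim 2) | 6.80 | 2.61 | 55% |
| 0.02 (assumed) | 24.18 | 4.92 | 31% |

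A simulation of skewed (lognormal) costs, with 3 against 3 and 6 against 6 hospitals, gave 80–83% coverage at ICC 0.001 and 55% at 0.005.

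**3. If hospitals are resampled instead.** With 3 hospitals per arm, the bootstrap variance of the mean is on average (3 − 1)/3 = 2/3 of what it should be. A normal-type interval then uses an effective critical value of 1.96 × √(2/3) = 1.60 where t on 4 df applies, and P(|t₄| < 1.60) is between 81% and 82%. This takes the hospitals as equally weighted. The hospital reading therefore does not rescue the interval.

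**4. Median against mean.** For an illustrative lognormal cost with a patient-level coefficient of variation of 1 (assumption), mean/median = exp(ln 2 / 2) = 1.41. The two cannot stand in for each other.

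**5. Cost inputs, side by side.**

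- *Pharmacist time.* The intervention consists of list audit, stability assessment and contact with providers. Only the last is costed, so this component is understated. The formula also pairs an hourly rate with minutes, so the units need stating.
- *Tests.* If the finance totals already contain the tests, adding them again in the intervention groups counts them twice. If the totals do not contain them, tests ordered in control hospitals go uncosted. Only one of these can occur, and the text does not say which situation applies.

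**The case against.** The strongest reply has four parts.

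- **The resampling unit is inferred.** The text nowhere says that patients are drawn, and a condensed article may leave the unit to the analysis plan. This stands, and the figures in step 2 are conditional on it. The alternative reading in step 3 also undercovers, however, and the median/mean contradiction does not depend on the unit.
- **Clustering is handled elsewhere.** A reader might infer that the cost analysis as a whole ignores hospitals. The documents do not support that: a mixed-effects model for total cost follows in the same section, and the trial's mixed models are described with a hospital intercept. With a log link, though, that model naturally yields a ratio, and the section does not say that a difference with an interval will be derived from it.
- **The ICCs belong to another outcome.** Correct. A reader might infer that the interval is far too narrow in any event, but the size depends on a cost ICC that the article does not give.
- **The cost inputs are ambiguous rather than wrong.** A reader might infer a biased cost difference. Double counting is possible but not shown; it would raise intervention cost, whereas omitted review time lowers it, so the net direction is unknown. Taking hourly salary times minutes as a 60-fold error reads loose drafting literally. What stands is that the discussion-only definition leaves out work the protocol itself describes.

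**Conclusion.** The point holds for the bootstrap step and for the definition of the cost inputs. The median/mean contradiction is certain. The lack of provision for hospitals is plain in the text; its consequence is conditional. With patient resampling and the protocol's ICCs for antibiotic days, the standard error is about 1.5 to 2.6 times too small and coverage is about 82% to 55%. With hospital resampling at three per arm and a normal-type interval, coverage is a little above 81%. The mixed model in the same section can account for hospitals, so the defect does not extend to the whole cost analysis.

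Three methods for cost are named across two sections (bootstrap, gamma mixed model, linear mixed model) and none is marked as the main one, so they could disagree with no rule for which prevails. Pharmacist cost is understated by an amount that the article does not allow one to calculate. For test cost, the finding is a risk of double counting or of unequal costing, not a demonstrated error.

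**What to change.** 1. Name the mean cost difference as the one cost estimand and remove the reference to medians.
2. Replace the bootstrap interval by one from the planned gamma mixed model, stating the hospital random intercept and a small-sample correction and reporting the marginal mean difference. Alternatively, analyse the 12 hospital means.
3. Reconcile this with the Data analysis plan sentence that assigns the linear mixed model to every continuous secondary outcome, by exempting total inpatient cost or by stating which model is the main one.
4. Cost tests once, from the same source and in the same way, in all 12 hospitals.
5. Cost all pharmacist time spent on the intervention, including list review and stability assessment, with time and salary in the same unit.

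The cost is a change of wording and a simple estimate of pharmacist review time; no new patient data are needed. The downside is a wider interval for the cost difference.
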